#### **P.2.c Plan for Specific Aim 3**

Incidence of allergy, doctor's diagnosis of eczema, and lower respiratory tract infection (LRI) at age 3 will be individually assessed. Like asthma and recurrent wheeze, two of the three secondary outcomes are dichotomous endpoints, and will be analyzed using logistic regression. For allergy, logistic regression will be used for specific IgE and linear regression will be used for log transformed total serum IgE level. Both a primary analysis of the relationship between vitamin D and the secondary outcome of interest will be conducted, as well as additional analyses including demographic and environmental risk factors for allergy, eczema, and LRI. The primary analysis, as well as additional analyses testing main demographic/behavioral effects and effect modification, will be conducted along the lines of analyses described for Specific Aim 2. The covariates to be considered for main effects and interaction analyses will be identical to those outlined for Specific Aim 2.

#### **P.2.d. Plan for Specific Aim 4**

This specific aim investigates the immediate and long-term impact of vitamin D supplementation on circulating 25(OH)D blood levels. The immediate impact of Vitamin D on 25(OH)D will be assessed through maternal plasma and cord blood measurements taken at delivery. The long-term influence will be examined via longitudinal analyses using children's blood measurements obtained at ages 1 and 3.

The hypotheses that 25(OH)D levels in maternal plasma and cord blood will be higher in the 4400 IU group will be tested using standard linear regression. If necessary, 25(OH)D levels will be transformed to meet the distributional requirements for the analysis. The 25(OH)D levels in maternal plasma and cord blood will be treated as separate outcomes, although both testing procedures for each analysis will be similar and are described jointly below. As with specific aims 1 and 2, the primary analysis will examine the relationship between 25(OH)D and vitamin D levels, while the secondary analysis will include other important demographic and

environmental factors related to 25(OH)D levels, such as climate and dietary vitamin D intake, testing for main effects and effect modification for these factors.

Letting  $y_i$  denote the 25(OH)D levels for each subject (as measured in mother's plasma for the first hypothesis, and cord blood for the second hypothesis), the model for the primary analysis is:

$$y_i = \alpha + \beta x_i + \gamma_1 a_{1,i} + \gamma_2 a_{2,i} + \varepsilon_i$$

where the covariates and parameters are as defined in Specific Aim 1. However, Specific Aim 3 tests the hypothesis that  $\beta=0$ , 25(OH)D levels do not significantly differ across the Vitamin D supplemented and control groups. All relevant covariates listed in Table 3 will be considered for the final model. For example, covariates measured post-natally would not be considered for inclusion in the analysis of maternal plasma or cord blood at delivery. Additionally, factors known to be directly associated with OH(25)D levels (i.e. sun exposure behavior, diet, ethnicity), will be included in the final model even if they are not statistically significant predictors of circulating vitamin D levels.

To assess modification of 25(OH)D levels by other demographic and behavioral variables, the model is:

$$y_i = \alpha + \beta x_i + \gamma_1 a_{1,i} + \gamma_2 a_{2,i} + \sum_k \delta_k Z_{ki} + \sum_k \eta_k x_i Z_{ki} + \varepsilon_i$$

where the parameters are as defined in Specific Aim 1. The  $k$  measured covariates for these analyses will be environmental, maternal, and child factors specific to 25(OH)D levels, such as sun exposure behavior, dietary intake of Vitamin D, and ethnicity. Additionally, any relevant covariates from Table 9 demonstrating main effects that have biologically plausible interactions with Vitamin D supplementation will be tested for effect modification. For both models, it is assumed that  $\varepsilon_i \sim N(0, \sigma^2)$ . The hypothesis that  $\delta_k=0$  will be used to examine whether any of these factors predict 25(OH)D levels, and the results will be used to adjust for any distributional imbalances of these factors across Vitamin D supplementation groups. As with the previous specific aims, we will also tests for effect modification via the hypothesis that  $\eta_k=0$ , or whether any maternal, child, or demographic/environmental covariates modify the relationship between vitamin D intake and circulating 25(OH)D levels in mother's plasma or cord blood. Additionally, we will follow the guidelines outlined in Specific Aim 2 to obtain the most parsimonious model.

The hypothesis that 25(OH)D levels in the child's blood will be higher in the 4400 IU group at birth, age 1 and age 3 will be tested using a repeated measures analysis framework such as generalized estimating equations.

#### P.2.d. Plan for Specific Aim 5

This specific aim investigates whether sufficient vitamin D supplementation in the pregnant mother is associated with reduced incidence of preterm birth (birth <37 weeks gestation) and/or preeclampsia, gestational hypertension, and/or HELLP syndrome compared to a usual care control group in VDAART.

The hypothesis that the incidence of preterm birth/preeclampsia, gestational hypertension and HELLP syndrome (PB/PE) is reduced in the high-dose vitamin D supplementation will be tested using logistic regression, allowing for fixed effect of center. Additional analysis will consider the modification of vitamin D exposure effects by maternal demographic/behavioral factors such as maternal age, BMI and weight gain during pregnancy, and maternal history of asthma/allergy, race, and other factors potentially associated with preterm birth/preeclampsia, gestational hypertension, HELLP or vitamin D exposure.

Letting  $M_i$  be an indicator function for the primary endpoint, PB/PE, for the  $i^{\text{th}}$  subject, the model is:

$$\text{logit Pr}(M_i = 1 | x_i, a_i) = \alpha + \beta x_i + \gamma_1 a_{1,i} + \gamma_2 a_{2,i}$$

where  $x_i$  denotes an indicator function for level of vitamin D supplementation (0=400 IU, 1=4,400 IU) in the  $i^{\text{th}}$  subject, while  $a_{1,i}$  and  $a_{2,i}$  are indicator functions for study center. The specific aim for this outcome tests the hypothesis that  $\beta=0$ , PB/PE incidence do not significantly differ across treatment groups, after adjusting for the potential effects of study center heterogeneity.

To assess modification of vitamin D exposure levels by other demographic and/or behavioral variables, the model is:

$$\text{logit Pr}(M_i = 1 | x_i, a_i) = \alpha + \beta x_i + \gamma_1 a_{1,i} + \gamma_2 a_{2,i} + \sum_k \delta_k z_{ki} + \sum_k \eta_k x_i z_{ki}$$

where  $z_{ki}$  represents the  $k$  measured covariates for each subject, and the other variables are as described above. This model addresses two hypotheses. First, main effects testing for behavioral/demographic covariates, or the hypothesis that  $\delta_k=0$ , will be used to examine whether maternal age, BMI, or other factors predict PB/PE. More importantly, inclusion of any significant main effects will adjust for any distributional imbalances of these factors across the vitamin D supplemented and placebo groups. Second, this model tests the hypothesis that  $\eta_k=0$ , or whether any maternal, child or demographic/behavioral covariates modify the relationship between vitamin D intake and our primary outcomes. To obtain a parsimonious model and limit multiple testing, only covariates with significant main effects and strong biologic plausibility for an exposure-dependent impact on PB/PE risk will be considered for interaction testing with vitamin D supplementation status. **Because of our fixed sample size we have chosen to combine PB and PE as our primary outcome.** Obviously we would like to explore the disease entities separately, and also examine the effect of race independent of vitamin D level. These analyses can be done using interaction terms and stratified analyses recognizing that we have lower power to detect these influences.

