
[name] trial has also generated more preliminary data regarding the response to the various doses of vitamin D. Figure 1 shows the response to varying doses of vitamin D in pregnant women from 3 ethnic groups: Caucasian (n=38 in Control group; n=37 in 2,400 IU, and n=39 in 4,400 IU), African American (n=24 in Control; n=35 in 2,400 IU; and n=26 in 4,400 IU), and Hispanic (n=45 in Control; n=48 in 2,000 IU; and n=44 in 4,000 IU). Baseline 25(OH)D levels varied by ethnic group, with African Americans having the lowest levels and Caucasians having the highest baseline levels. The 2400 IU/day dose raised the circulating 25(OH)D levels to a mean of about 95 nmol/L, and only approximately 60% achieved levels of >75 nmol/L. The 4400 IU/day dose most rapidly and consistently increased 25(OH)D levels in the participants from all ethnic groups, with a mean of about 112 nmol/L, and practically all participants achieved levels of at least 75 nmol/L. Additionally, the 4400 IU/day dose eliminated all seasonal variation in circulating 25(OH)D levels. There were no instances of adverse events from the 4000 IU/day dose, either in the mother or the infant, even in those mothers whose beginning 25(OH)D levels were > 75 nmol/L. **Thus, 4400 IU/day of vitamin D was the dose that achieved sufficient supplementation in the pregnant women. The preliminary results and experience from [name] clinical trials have provided valuable information for our current proposal, regarding the dosing and safety of vitamin D supplementation in pregnancy.**

**TABLE 1. Summary of published high-dose vitamin D supplementation studies in healthy adults and pregnant and lactating women\*. Adapted from Hollis and Wagner**

| Reference†                                              | Subject type                | No. of subjects                         | Vitamin D dose                  | Therapy duration | Initial 25(OH)D                  | Endpoint 25(OH)D                   | Actual change in 25(OH)D    |
|---------------------------------------------------------|-----------------------------|-----------------------------------------|---------------------------------|------------------|----------------------------------|------------------------------------|-----------------------------|

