**F. Measurement of 25(OH)D**

Blood will be drawn from the mothers at randomization, at the in-person research prenatal visit at 32-38 weeks gestation, and at 1 yr after delivery. Cord blood will also be collected at delivery. Blood from the child will be collected at 1 yr and at 3 yrs. All specimens will be shipped to the DCC, where they will be logged in and processed. Measurement of 25(OH)D will be performed at the Channing Laboratory DCC as previously described. Twenty five (25) microliters of serum or plasma (EDTA or Heparin) is required for the 25-OH-D extraction, however, 100 microliter samples will be aliquoted to allow for duplicate measurements on each sample. A chemiluminescence assay will be employed. The LIAISON® 25 OH Vitamin D assay (DiaSorin, Inc., Stillwater, MN) is a direct competitive chemiluminescence immunoassay (CLIA) for quantitative determination of total 25 OH vitamin D in serum or plasma. During the first incubation, 25 OH Vitamin D is dissociated from its binding protein and binds to the specific antibody on the solid phase. After 10 minutes the tracer, (vitamin D linked to an isoluminol derivative) is added. After a second 10 minute incubation, the unbound material is removed with a wash cycle. Subsequently, the starter reagents are added to initiate a flash chemiluminescent reaction. The light signal is measured by a photomultiplier as relative light units (RLU) and is inversely proportional to the concentration of 25 OH vitamin D present in calibrators, controls, or samples. In order to monitor assay performance each assay will include one quality control sample. The control will be treated as unknown specimen and multiple (5) determinations will be made. Assay variation will be determined and acceptable performance limits will be defined as ≤15 C.V. In addition 20% of the samples will also be re-measured in [name] laboratory in the Medical University of South Carolina.

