#### **P.2.b. Plan for Specific Aim 2**

For this analysis, our N will be 800, since most of the dropouts will be expected to occur after delivery. Thus, the expected drop in N due to the 8% miscarriage rate was applied. We will test the hypothesis that the dose of 4,400 IU per day is sufficient to get 90% of the women to a sufficient level of 25(OH)D of at least 75 nmol/L, primarily using a logistic regression model, with randomization group (i.e. intervention group vs. usual care) as the independent variable. The dependent variable will be 25(OH)D level at delivery. We will adjust our analyses for other covariates that may affect 25(OH)D level, such as sun exposure (from the SmartProbe and the sun exposure questionnaire), age, and diet (calculated vitamin D intakes from dietary sources).

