**Table 6. Power to detect a 25-35% reduction in secondary outcomes for 870 subjects in a multi-site study, (effectively 660 patients, assuming an 8% miscarriage rate and 18% loss to follow-up)**

| Mean Incidence of secondary outcome in 400 IU group | Percent reduction in secondary outcome in 4400 IU group |            |            |
|------------------------------------------------------------|----------------------------------------------------------------|------------|------------|
|                                                            | 35%                                                     | 30% | 25% |
| 0.50                                                | 0.998                                                          | 0.982      | 0.913      |
| 0.45                                                | 0.992                                                          | 0.958      | 0.858      |
| 0.40                                                | 0.973                                                          | 0.906      | 0.779      |
| 0.35                                                | 0.936                                                          | 0.845      | 0.691      |
| 0.30                                                | 0.890                                                          | 0.736      | 0.608      |
| 0.25                                                | 0.795                                                          | 0.654      | 0.531      |

**Q.4. Power for Specific Aim 4.** The research to date on the impact of vitamin D supplementation on 25(OH)D is presented in Table 1. As noted in the table, only 4 studies have been conducted on pregnant women, all had fewer than 100 subjects, and the maximum daily dose for these studies was 1,600 IU. The only data available on 25(OH)D status in the supplementation ranges we are proposing has been provided by [name] (unpublished data, see section III). In a study of 347 pregnant women (African Americans, Hispanic,

and Caucasians) on either 4000 IU (supplemented) or 400 IU (control) of Vitamin D daily, the maternal plasma 25(OH) D levels were 115 nmol/L in supplemented subjects, and 80 nmol/L in controls after 8 months of supplementation, an overall difference of 35 nmol/L. The estimated standard deviation for 25(OH)D levels in these ranges is 40.

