Based on the observed differences/variation in 25(OH)D levels, we used simulation studies to estimate the power to detect a mean difference of 7.5 – 37 nmol/L across the supplemented and control groups in maternal plasma at 26-28 weeks, as well as maternal plasma and cord blood at delivery, using an estimated standard deviation of 40. We anticipate that the difference in 25(OH)D levels in maternal plasma across treatment groups will be less

pronounced at the 26-28 week measurement period (e.g., 12.5 – 25 nmol/L), and we do not expect to observe a significant difference by supplementation status in circulating vitamin D in infants at 1 and 3 years of age, since no post-natal treatment intervention is planned. The simulations were generated in a similar manner to method described for Specific Aim 2, except that linear regression (rather than logistic) was used to model the relationship between circulating vitamin D and vitamin D supplementation status. Study heterogeneity was incorporated into the model by allowing 25(OH)D levels to vary by 25 nmol/L across study sites. Since this phenotype will be measured five times throughout the study period, the power was defined as the proportion of replicates with a Wald test statistic (i.e., testing the null hypothesis that the coefficient for vitamin D supplementation status is 0) 2-sided p-value was less than 0.01 (0.05/5). Additionally, this specific aim will include 2 interim and a final analysis, which will be identical to the procedure outlines for specific aim 2. While the power estimates below do not directly incorporate the interim looks, we feel that the power reduction will be modest. The results are shown in Table 7.

**Table 7. Power to detect a 7.5 – 37 nmol/L difference in 25(OH)D for 870 subjects in a multi-site study, (effectively 660 patients, assuming an 8% miscarriage rate and 18% loss to follow-up).**

| Mean change in 25(OH)D levels in 4400 IU group (nmol/L) | Power |
|---------------------------------------------------------|-------|
| 7.5                                                     | 0.444 |
| 12.5                                                    | 0.925 |
| 25                                                      | 0.999 |
| 37                                                      | 0.999 |

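### The Aim 4 primary models for maternal and cord-blood 25(OH)D adjust for centre only and leave out the mother's enrolment 25(OH)D, so their intervals may be wider than they need be

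*Supplement*

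**What the plan says.** The Aim 4 plan (Current Protocol, P.2.d) writes out its primary model: 25(OH)D regressed on a treatment indicator and two centre indicators. Maternal and cord-blood levels are separate outcomes. For the adjusted analysis, the covariates in Table 3 are candidates, and "factors known to be directly associated with OH(25)D levels (i.e. sun exposure behavior, diet, ethnicity), will be included in the final model" whether or not they reach significance. The same section gives climate and dietary intake as examples of factors for the secondary analysis.

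The Aim 2 plan (P.2.b) uses logistic regression for reaching 75 nmol/L. It says "We will adjust our analyses for other covariates that may affect 25(OH)D level, such as sun exposure (from the SmartProbe and the sun exposure questionnaire", and goes on to age and diet.

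On sampling, VI.F says "Blood will be drawn from the mothers at randomization, at the in-person research prenatal visit at 32-38 weeks gestation". The enrolment-visit text in section V also has blood stored for this assay.

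Enrolment 25(OH)D is not in Table 3, nor in either list above. The Addendum to Analysis Plan (II.A) does use baseline levels, but only to relate them to trial outcomes and to form joint high/low groups. It does not use them to adjust the treatment contrast on later 25(OH)D.

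**The concern.** The adjusted model forces in indirect determinants of vitamin D status but not the pre-dose value of the same analyte. The protocol itself reports that women start from different levels. Of the earlier supplementation trial, section III says "Baseline 25(OH)D levels varied by ethnic group, with African Americans having the lowest levels and Caucasians having the highest baseline levels". Section IV also enrols women whose levels are already normal. Adjusting for ethnicity removes only the part of this spread that lies between groups.

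If enrolment level predicts later level within arms, an analysis that omits it leaves explainable variance in the error term. At stake is the width of the interval for the maternal and cord-blood differences, and power if the true difference were near the bottom of the range tabulated in Q.4.

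**Working it through.** **Inputs, all from Q.4.**
- SD: "using an estimated standard deviation of 40" nmol/L.
- Sample: "effectively 660 patients, assuming an 8% miscarriage rate and 18% loss to follow-up", hence 330 per arm.
- Alpha: 0.05/5 = 0.01, two-sided, for five 25(OH)D analyses.
- Expected maternal effect: 115 against 80 nmol/L, "an overall difference of 35 nmol/L".
- Within-arm correlation r: not given in the documents. I assume 0.3, 0.5 and 0.7.

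**Step 1: reproduce Table 7.**
- SE = 40 × sqrt(2/330) = 3.114.
- Power = Φ(d/SE − 2.576).
- At d = 7.5: Φ(2.408 − 2.576) = 0.434. Table 7 gives 0.444.
- At d = 12.5: Φ(4.014 − 2.576) = 0.925. Table 7 gives 0.925.
- At 25 and 37 nmol/L power exceeds 0.999, as tabulated.
- Using 400 per arm, or alpha 0.05, does not reproduce the first two rows (0.530 and 0.673 at 7.5 nmol/L).

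The stated power therefore takes no credit for a baseline covariate.

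**Step 2: add enrolment 25(OH)D to the linear model.** The residual SD becomes 40 × sqrt(1 − r²), and the 95% half-width is 1.96 × SE.

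| r | Variance removed (r²) | Residual SD | SE | 95% half-width | Power at 7.5 | Power at 12.5 | Equivalent n per arm, 330/(1 − r²) |
|---|---|---|---|---|---|---|---|
| 0 | 0% | 40.0 | 3.11 | 6.10 | 0.434 | 0.925 | 330 |
| 0.3 | 9% | 38.2 | 2.97 | 5.82 | 0.480 | 0.949 | 363 |
| 0.5 | 25% | 34.6 | 2.70 | 5.29 | 0.581 | 0.980 | 440 |
| 0.7 | 49% | 28.6 | 2.22 | 4.36 | 0.787 | 0.999 | 647 |

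At 35 nmol/L power exceeds 0.999 in every row. There the gain is interval width alone.

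**Step 3: season of draw.** If season explained 2% to 10% of the variance (again an assumption), the SD would be 39.6 to 37.9 and power at 7.5 nmol/L 0.443 to 0.485. That is a small gain.

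**Step 4: does the same argument carry to Aim 2?** I simulated 600 trials per value of r, with 400 per arm, means 80 and 115, SD 40 and a cut at 75 nmol/L. Adding baseline to the logistic model gave these averages:

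| Model | Log odds ratio | SE | Wald z |
|---|---|---|---|
| Unadjusted | about 1.48 | 0.171 | about 8.6 |
| Adjusted, r = 0.3 | 1.56 | 0.177 | 8.8 |
| Adjusted, r = 0.5 | 1.74 | 0.190 | 9.1 |
| Adjusted, r = 0.7 | 2.16 | 0.223 | 9.6 |

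The standard error rises. The test gains because the conditional odds ratio lies further from 1 than the marginal one. Every cell of Table 5 (Q.2) already has power above 0.999.

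**The case against.** The strongest reply is that a treatment-plus-centre model is valid, simple and amply powered for the effect the trial expects. All of that stands. The size of the gain also rests on a correlation that the documents do not supply. The background section does cite a strong maternal-newborn correlation, but that does not establish one between a sample at 10-18 weeks and cord blood months later, after randomized supplementation.

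A second reply is that the covariate lists are partly open: Aim 2 gives its covariates as examples, and the Aim 4 effect-modification text does the same. This helps the adjusted analyses, where enrolment level could be brought in. It does not help the Aim 4 primary model, whose equation is explicit and closed.

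A reader might infer more than the documents support:
- **That the contrasts are biased, or that a chance imbalance must go uncorrected.** Randomization is blocked within site and race/ethnicity, and the open lists would permit adjustment. The fair statement is that enrolment level is not named.
- **That Aim 2 is also estimated less precisely than it could be.** Step 4 shows that adjustment raises the standard error of the log odds ratio and changes what is estimated.
- **That power is being lost for the child at ages 1 and 3.** Q.4 expects no significant difference there, and nothing suggests that maternal level in early pregnancy predicts the child's level years later.
- **That season is ignored.** Climate is named for the Aim 4 secondary analysis, sun exposure is forced into the adjusted model, and the sun questionnaire (VI.I) asks about summer and winter. What is missing is a season or date-of-draw term by name.

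**Conclusion.** The point holds for the Aim 4 primary models of maternal and cord-blood 25(OH)D. They omit a pre-treatment measurement of the outcome analyte that the trial already collects, and the adjusted model does not name it either. For r between 0.3 and 0.7, including it would remove 9% to 49% of the residual variance and bring the 95% half-width from 6.10 down to between 5.82 and 4.36 nmol/L. Power would change materially only for differences near 7.5 nmol/L, well below the 35 nmol/L expected in maternal plasma. At 12.5 nmol/L it is already 0.925.

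These figures assume the plan's SD and numbers, a linear relation, and one correlation common to both arms. A lower correlation, which is plausible for cord blood, would give a smaller gain. This is an inexpensive improvement in efficiency; it corrects no bias and no shortage of power at the planned effect.

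**What to change.** In P.2.d, add continuous maternal enrolment 25(OH)D to the primary models for maternal and cord-blood 25(OH)D, and state a simple rule for women with no enrolment value (for example, single imputation that ignores arm, plus a missingness indicator). Say which late-pregnancy maternal sample the model applies to: P.2.d speaks of delivery, whereas VI.F schedules the draw at 32-38 weeks.

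Optionally, name season of draw, derived from the draw date, in the adjusted Aim 4 model beside climate and sun exposure.

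In P.2.b, enrolment 25(OH)D may be added to the logistic model for power and to handle chance imbalance, provided the plan states whether the reported odds ratio is conditional or marginal. A smaller standard error should not be given as the reason.

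The cost is about one sentence per section. No new sample or assay is needed.
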